#### Semistructured interviews with patients

Patients allocated to EG will be offered the opportunity to participate in one semistructured interview after intervention finalisation. They will be informed about and asked for participation during the third or fourth week of the VR training intervention. The face-to-face interview will take between 30 to 60 minutes and will be conducted at the place of the patient’s convenience, either at the treating clinic or at the patient’s home. To provide a high level of privacy, all interviews will take place in a separate and quiet room. Participation will be voluntary, and all interviews will be voice-recorded.

A purposive sampling method will be employed according to the patients’ experienced phenomenon of interest [31]. It is proposed to include a sample of about ten patients to explore and to describe in detail experiences and new knowledge gained in a particular field [32].

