The current study includes two parts: (1) a quantitative investigation of the efficacy of virtual reality training compared to conventional therapy in upper-limb motor function are investigated, (2a) a qualitative investigation of patients’ experiences and expectations of virtual reality training and (2b) a qualitative investigation of therapists’ experiences using the virtual reality training system in the therapy setting.

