#### Sample size and statistical analyses

On the basis of a study on the efficacy of an earlier study in which the investigators tested the VR system in children with cerebral palsy [29], a power analysis and sample size calculation for the present study were performed with G*Power software version 3.1.5 [30]. In the cited study of children, the BBT (primary outcome measure) showed an effect size (Cohen’s *d*) of 0.98. Assuming a similar effect size for adult stroke patients, we would need (two-tailed test, power = 0.9, significance level *P*-value = 0.05) a total of 46 patients (23 per group). Assuming a dropout rate of 20%, we will recruit a total of 60 patients across the participating centres.

Data will be analysed qualitatively and quantitatively for each patient separately. Changes will be provided as a total number or percentage. Group comparisons between EG and CG will be analysed using analysis of covariance after assessment of normal distribution. We intend to perform an intention-to-treat analyses. If necessary, an additional per protocol analysis will be carried out. Furthermore, subgroup analyses will be performed to investigate any possible study site effects. Patients’ training settings (nominal and interval data) will be analysed with frequencies and percentages to describe therapy content and provide recommendations for further therapy settings.

All study personnel will try to avoid patient dropouts. However, patients can leave the study at any time without reason. Collected patient data until the point of dropout will be included in the final analysis. Missing data will be replaced using two different approaches: (1) with the last available value carried forward method and (2) by adding or subtracting the mean difference of other patients in the respective group. Analysis with both approaches will be performed.

### Part 2

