#### Focus groups with therapists

Therapists treating patients with the VR training system will be offered the opportunity to participate in a focus group session that will last from 1 to 2 hours. Therapists will be informed about and asked for participation after they have completed at least one series of patient training with the VR training system, including 16 training sessions or a comparable number of training sessions with different patients. The focus group sessions will be conducted at one of the participating clinics, and three to six therapists will participate in one focus group. Participation will be voluntary, and all interviews will be voice-recorded.

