#### Overall ethical considerations and reporting of adverse events

The VR training system is a commercial product sold under the name YouGrabber. It uses VR to train upper-limb motor function. It has been available (initially as a beta version) for testing purposes in clinics since 2010 and has been used in rehabilitation institutions and pilot clinical studies with no safety-related incidents. Nevertheless, patients might experience negative emotions or have the impression that they cannot perform the training tasks because of their reduced motor function. It is expected that study participation will take a lot of patients’ time in both groups. The following measures will be utilized in exchange for the patients’ time exposure in the current study:

Patients will be assessed on a regular basis to evaluate their rehabilitation process.Patients will have an intensive therapy schedule with four therapy sessions per week over the course of 4 weeks.Patients will have the opportunity to learn about an innovative VR training system.Patients can withdraw from the study at any time without giving a reason.

The study will be carried out in accordance with the protocol, with the guidelines for good clinical practice and current national and international valid legal provisions. Any adverse event will be reported to the responsible ethics committee directly and will be mentioned in intermediate and final study reports. The study is registered in the Clinicaltrials.gov trials database with the identifier NCT01774669.

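### Experimental-group patients who stop VR training in week 1 or 2 have no described route to the patient interview

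*Protocol article*

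**What the plan says.** All references are to the Protocol article.

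- **Offer and timing** (Semistructured interviews with patients). The offer is broad: "Patients allocated to EG will be offered the opportunity to participate in one semistructured interview after intervention finalisation". The next sentence ties it to a point in training: "They will be informed about and asked for participation during the third or fourth week of the VR training intervention".
- **Sampling** (same section). "A purposive sampling method will be employed according to the patients’ experienced phenomenon of interest", and "It is proposed to include a sample of about ten patients". No criterion is given for patients who stopped early.
- **Patients who leave** (text below Table 3). They are still invited to every planned measurement event, with the same assessments as other participants. The interview is not listed in Table 3.
- **Purpose** (Discussion paragraph of the Abstract, Background, and the opening of Part 2). The interviews are to support recommendations for routine use of the VR system, help improve it, and help formulate treatment guidelines.
- **Exposure** (Table 2, item 4, and Overall ethical considerations). Training runs at four sessions a week for 4 weeks. By the end of the second VR session a patient should have tried every application and all three movement modes.
- **Foreseen difficulties** (Overall ethical considerations). "patients might experience negative emotions or have the impression that they cannot perform the training tasks because of their reduced motor function". Criteria for halting the trial adds shoulder pain and cybersickness.

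**The concern.** The invitation rule works as a selection rule. A patient is first asked only if still in VR training in the third week, so patients whose training ended before then are outside the pool from which the purposive sample is drawn. Those who gave up early because the tasks were too hard, frustrating or uncomfortable could tell the investigators most about when the system should not be used, or how it should be changed.

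At stake is the scope of the Part 2 recommendations. If the interviews contain only patients who tolerated at least half the course, a theme that occurs mainly among early stoppers may be missing from the patient accounts, and a reader could not tell its absence from its not existing.

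**Working it through.** **1. The plan's own figure.** Sample size and statistical analyses uses d = 0.98, two-sided alpha 0.05 and power 0.90. A two-sample t-test calculation gives n = 22.89, so 23 per group and 46 in total, with power 0.901 at 23 per group. Inflating for dropout gives 46 / 0.8 = 57.5, so 58; the plan recruits 60. The figure reproduces and is not in dispute. It is used here only as the source of the number of patients and the dropout rate: "Assuming a dropout rate of 20%, we will recruit a total of 60 patients across the participating centres".

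**2. Exposure when the invitation window opens.** Two weeks at four sessions a week is 2 x 4 = 8 sessions, and 8 / 16 = 50% of the course for a patient on schedule.

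**3. Is there another way in?** Setting the passages side by side:
- The interview section gives one invitation point, weeks 3 to 4 of training.
- The rule for leavers covers the Table 3 assessments only.
- Criteria for halting the trial provides that patients meeting those criteria are evaluated, assessed and followed up. It mentions no interview.
- Purposive sampling can select only from those who are asked.

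None of these reaches a patient who stopped in week 1 or 2.

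**4. Has such a patient experienced enough to be worth interviewing?** By Table 2, item 4, yes: someone who stops after the second session should already have tried all applications and modes.

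**5. How many patients?** Assumptions: equal allocation, so 60 / 2 = 30 in EG; the 20% dropout applies to EG and stands in for stopping VR, so 0.20 x 30 = 6 leavers. The plan does not say when they leave, so a range is needed. For the even-spread case, 4 weeks of training plus 2 months of follow-up is taken as about 13 weeks.

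| Timing of the 6 EG leavers (assumed) | Never asked | Share of EG | Equivalent in a proportional sample of ten |
|---|---|---|---|
| Spread evenly over about 13 weeks | 6 x 2/13 = 0.9 | 3% | 0.3 |
| Half before week 3 | 6 x 0.5 = 3 | 10% | 1 |
| All before week 3 | 6 x 1 = 6 | 20% | 2 |

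The range is about 1 to 6 patients. The last column only gauges size, because the sample is purposive and not proportional.

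**The case against.** The strongest reply is that Part 2 is descriptive phenomenology with purposive sampling, not an estimate of prevalence, so a share of the arm is the wrong yardstick and wanting interviewees with substantial exposure is defensible. The first half stands: the percentages show how many patients are affected, not a bias in an estimate. The second half is weaker, because the plan itself expects full exposure to the system's applications and modes by session 2 and states no minimum-exposure reason for the timing.

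A second reply is that 20% dropout covers the whole trial for any reason, so few may leave in the first two weeks. This stands, and it is why the range starts at about 1.

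Several stronger readings are tempting but are not supported:

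- **That therapists are selected in the same way.** The focus-group section says "Therapists will be informed about and asked for participation after they have completed at least one series of patient training with the VR training system", but it goes on to accept a comparable number of sessions with different patients. A therapist whose patients stopped early can therefore qualify once sessions add up, and can describe those patients, though only indirectly.
- **That the single late interview defeats the expectations objective.** The Background announces "a qualitative investigation of patients’ experiences and expectations of virtual reality training", but the Part 2 aim is worded as experiences and expectations during the intervention, and no pre-treatment measure is promised. The listed questions are only examples; the full guide is in an additional file that is not shown.
- **That only near-completers are heard.** At invitation a patient may have done just 8 of 16 sessions, and nothing withdraws the interview from someone who stops after being invited.
- **That the foreseen negative experiences are removed.** The plan says patients may have them, not that they leave. Those who struggle but are still training in week 3 can be interviewed, and one example question asks about concerns with the system. Adverse events are reported separately.

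**Conclusion.** The point holds in a limited form. As described, EG patients who stop VR in week 1 or 2 cannot be among the interviewed, and the patient interviews are likely to under-represent reasons for early stopping. A reader might infer that the qualitative result will make VR look more acceptable than it is. The document does not support that certainty: the direction is plausible, but the size depends on how many stop early and why, and neither is known.

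The size is roughly 1 to 6 EG patients never asked, assuming 30 in EG, 20% dropout in that arm, and dropout as a stand-in for stopping VR. If nobody stops before week 3, nothing is lost. Part 1, including the sample size and the primary comparison, is unaffected. This is an inexpensive improvement to the qualitative part, not a threat to the trial's main conclusion.

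**What to change.** Change the section Semistructured interviews with patients so that:

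1. EG patients are told about the interview at the start of VR training.
2. They are invited at the end of VR training or on leaving it, whichever comes first.
3. The sample of about ten purposively includes patients who stopped early, if there are any.

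Because only EG patients are interviewed, someone other than the blinded assessor should make the invitation to those who leave early.

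The sample size of the interviews does not change and no assessment is added. The cost is protocol wording and an ethics notification. The modification route under Methods and design, which is written for eligibility criteria and therapy content, asks for agreement of all centres and approval by the ethics committees, and the sponsor may choose to follow it here. Some early leavers will decline, as participation is voluntary. Since the trial is already recruiting, the change may help only patients not yet past the early weeks; the report should then say that earlier stoppers were not asked.

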#### Interview guide semistructured interviews

Semistructured interviews consist of open-ended questions [33]. The loose structure allows the opportunity to explore and follow an idea deeper without a preimposed interview structure [33]. It is intended to provide an in-depth description of the explored phenomenon [34]. On the basis of existing literature, an interview guide has been developed [35]. The guide divides the interview into three parts (see Additional file 1):

Welcoming, information about the interview procedure, questions regarding the rehabilitation process and querying the patient’s current condition.Questions regarding the main research question, such as, What do you think about the VR intervention? How did you feel during the intervention? What were your concerns related to the training system? How did you experience the role of the therapist during the VR training?Interview summary by the interviewer, final remarks of the patient and farewell.

#### Focus groups with therapists

Therapists treating patients with the VR training system will be offered the opportunity to participate in a focus group session that will last from 1 to 2 hours. Therapists will be informed about and asked for participation after they have completed at least one series of patient training with the VR training system, including 16 training sessions or a comparable number of training sessions with different patients. The focus group sessions will be conducted at one of the participating clinics, and three to six therapists will participate in one focus group. Participation will be voluntary, and all interviews will be voice-recorded.

#### Interview guide focus groups

Similar to the semistructured patient interviews, the focus group questions will be open-ended [33]. The guide for the focus groups divides the interview into three parts (see Additional file 2):

Welcoming, information about the interview procedure, introduction of focus group participants and taking general questions on the VR training experience.Questions regarding the main research question, such as, How did you experience the patient during the VR training? How did you experience the patient’s motivation? How did you feel during the training with VR?Interview summary of the interviewer, final remarks of the participants and farewell.

Semistructured interview and focus group questions were tested with two patients and therapists beforehand to check for comprehensibility and clarity and were reviewed by the responsible ethics committees.

#### Data analysis of semistructured interviews and focus groups

In addition to the voice-recording of the interviews and focus groups, interviewers will write field notes to describe the interview situation: the way the patient acts during the interview, the patient’s mood and feelings, the course of the interview, unexpected events or statements, and the feelings and impressions of the interviewer. Field notes and the interview and focus group content will provide the basis for the data analysis, which will be based on a descriptive phenomenological approach without data or opinion interpretation [36]. Data analysis will include three steps:TRANSCRIPTION (step 1): Interview content will be transcribed verbatim.CONDENSATION (step 2): Patients’ and therapists’ quotes will be summarised to highlight the main statement.CODING and CATEGORISATION (step 3): On the basis of the thematic analysis, categories and codes will be created to sort patients’ and therapists’ statements [37]. This can be done with the help of a qualitative data analysis tool such as NVivo [38] or ATLAS.ti [39].

#### Overall ethical considerations and reporting of adverse events

The VR training system is a commercial product sold under the name YouGrabber. It uses VR to train upper-limb motor function. It has been available (initially as a beta version) for testing purposes in clinics since 2010 and has been used in rehabilitation institutions and pilot clinical studies with no safety-related incidents. Nevertheless, patients might experience negative emotions or have the impression that they cannot perform the training tasks because of their reduced motor function. It is expected that study participation will take a lot of patients’ time in both groups. The following measures will be utilized in exchange for the patients’ time exposure in the current study:

Patients will be assessed on a regular basis to evaluate their rehabilitation process.Patients will have an intensive therapy schedule with four therapy sessions per week over the course of 4 weeks.Patients will have the opportunity to learn about an innovative VR training system.Patients can withdraw from the study at any time without giving a reason.

The study will be carried out in accordance with the protocol, with the guidelines for good clinical practice and current national and international valid legal provisions. Any adverse event will be reported to the responsible ethics committee directly and will be mentioned in intermediate and final study reports. The study is registered in the Clinicaltrials.gov trials database with the identifier NCT01774669.

#### Quality control and quality assurance

To achieve and maintain a high quality standard during study preparation and implementation, the following measures will be employed:

Comprehensive training for all study therapists to use the VR training system before study start.Comprehensive training for all study therapists to perform all necessary outcome measures before study start.Three refresher training days for VR system training and assessment performance throughout the studyStudy management updates for all centres on a regular basis (monthly).Daily telephone and email access for technical support.

Furthermore, up to three monitoring events will be performed for each participating study centre. An authorised person from the sponsor, which is not involved in patient treatment or assessments, will visit the clinics and inspect data handling and patient organisation. Up to five randomly selected patient data files will be inspected.

All study-related patient data will be entered directly onto the anonymised case report forms or assessment scoring sheets. Study-related original patient documents will remain in the responsible clinic and will be archived for 10 years. After that period, patient documents will be destroyed in accordance with the clinic’s data destruction guidelines. Only anonymised electronic data or paper copies will be sent to the study coordinator for data analyses.

Training data collected via the VR training system will be saved in anonymised form under the patient’s study ID, with no other identifying information. Data backup and synchronization will be carried out using a secure, encrypted data transfer and storage framework.

#### Dissemination policy

The study personnel will adhere to an open access policy:

The trialists intend to publish the study protocol and the study results in international open access journals to provide easy access to the study documents for all interested readers.The study is registered in an international open access clinical trial database (Cliniclatrials.gov Identifier: NCT01774669).As the study progresses, its methods and preliminary results will be presented at national and international congresses and workshops.After study finalisation and data analyses, all study patients will receive a plain language summary of the study results, and the results will be presented in each participating clinic.

Involvement of professional writers is not intended. No restrictions will be placed on the publication of positive or negative results. The study results will be reported in accordance with the guidelines set forth in the 2010 Consolidated Standards of Reporting Trials (CONSORT) [40].

#### Criteria for halting the trial

At present, the commercial YouGrabber system has been used for more than 2 years with over 100 patients in different acute hospitals and rehabilitation clinics. So far, no adverse events have been reported. However, this study will be halted if any of the following criteria are fulfilled:

More than three EG patients report a sudden onset of or increase in shoulder pain during or just after therapy that is highly likely to be attributable to the use of YouGrabber, and which does not immediately cease after stopping therapy (evaluated as ≤3 on the Chedoke-McMaster Stroke Assessment subscale pain).More than 50% of EG patients (minimum of five patients) report severe cybersickness during YouGrabber training which persists after training is halted.EG patients show an unexpected decrease in motor function (change of three or more levels in the Chedoke-McMaster Stroke Assessment) indicating a highly significant difference between therapies with YouGrabber compared to conventional therapy.Epileptic seizures in at least two patients are induced directly while using YouGrabber.

Patients reporting the criteria mentioned above will be evaluated by the physician on duty and will be assessed and followed up for the originally planned study duration.

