**Table 1 Tab1:** **Patient selection criteria**

Inclusion criteria	Exclusion criteria
• ≥6 months after first-ever stroke (ischaemic, haemorrhagic)	• Previous or current other functional deficits of arm and hand motor function not due to stroke
• Able to sit in a normal chair without armrests and without support of the back rest	• Severe cognitive deficits: Mini-Mental State Examination score ≤20
• Persistent motor deficit of arm and hand confirmed by Chedoke-McMaster Stroke Assessment arm subscale level ≥3 and hand subscale level ≥2 (The difference between both subscales has to be two levels or more.)	• Severe visuospatial disorders (for example, severe visual neglect confirmed by LineBisectionTest)
• Able to score at least 1 on the Box and Block Test (main outcome measure)	• History of epileptic seizures triggered by visual stimuli (for example, television, video games) within the past 6 months

The patient recruitment strategy employs different approaches:Patients will be recruited from the clinics’ inpatient or outpatient departments by physicians, therapists and nurses.Patients will be recruited from the clinics’ patient database. Datasets will be screened for study selection criteria by the involved study personnel. If patients are eligible, they will receive a letter describing the study and including patient information. If patients are interested in participating, they can contact the study personnel in the responsible clinic by telephone, postal mail or email.Patients will be recruited via a study information flyer provided on each clinic’s homepage and through patient self-help groups. If patients are interested in participating, they can contact the study personnel in the responsible clinic by telephone, postal mail or email.

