#### Outcome parameters and related outcome measures

Table 3 provides an overview of all outcome measures and measurement events. All data will be collected on a case report form (CRF) that will be stored in a locked cabinet and will not be accessible by the treating therapist. The standardised CRF can be obtained from the first author ([name]).

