#### Secondary outcomes: upper-limb activities of daily living and motor and cognitive function

Upper-limb ADL and motor and cognitive function are secondary outcomes. They will be assessed objectively with the Chedoke-McMaster Stroke Assessment (CMSA), the Chedoke Arm and Hand Activity Inventory (CAHAI) and the Line Bisection Test (LBT) and subjectively with the Stroke Impact Scale (SIS).

The CMSA was developed by Gowland *et al*. in 1995 for the evaluation of physical impairment and activity level of stroke patients [15]. In the present study, we will use the impairment subscales for hand and arm function. Patients will be scored on a seven-point scale (1 = hypoactive or absent muscle reflexes, 7 = no functional impairment detectable anymore, prestroke status) according to seven stages of motor recovery [16]. Additionally, shoulder pain of the affected body side will be evaluated on the same seven-point scale using another subscale. The CMSA has been shown to be a valid and reliable assessment tool [15, 17].

The CAHAI was developed by Barreca *et al*. in 2004 [18–21]. It contains 13 real-life items scored from 1 to 7 (highest score). For example, one item is putting toothpaste on a toothbrush. Scores represent the patient’s relative ability to independently perform stabilisation or manipulation in ADL with the affected upper limb. A score of 1 represents total dependence on another person, and a score of 7 indicates patient independence without time or safety concerns or necessary splints or devices. The test’s reliability and validity have been evaluated [20, 21].

The LBT is a paper-and-pencil test used to evaluate the presence of unilateral spatial neglect (USN) [22]. Patients are asked to mark the centre of a drawn line on paper with a pencil. This is repeated for 18 lines on a sheet of paper. A deviation of more than 6 mm from the centre in the upper and lower 9 lines indicates the presence of USN.

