## Discussion

The aim of this multicentre trial is to determine the efficacy of a VR-based upper-limb training programme compared to conventional occupational therapy and physiotherapy. Additionally, the users’ perspectives will be evaluated by conducting semistructured patient interviews and therapist focus groups.

In the rapidly evolving VR training industry, it is important to develop a detailed perspective on different aspects of the training interventions used, based on the patients’ and therapists’ perceptions. This goal will be achieved by using a mixed-methods design combining quantitative and qualitative research methods. In particular, from the qualitative data, new hypotheses for further research and adaptations will emerge, including training recommendations and system modifications.

In addition, the knowledge gained in the present study will contribute to the trends described in the review by Laver *et al*. [2]. On the basis of their systematic review of the literature reaching back to March 2010 or earlier, they claimed that the most beneficial patient and VR system characteristics are still undetermined.

The design of a multicentre study offers several advantages and challenges. The shared patient recruitment and treatment methodology provides the opportunity to conduct a sufficiently powered trial to reduce the risk of type I error [41]. Also, therapists and patients from various clinics and different parts of Switzerland can evaluate the VR training options according to personal preferences and local conditions.

In the present study, we decided to use only one randomisation list that will be stored in the pharmacy at one of the three clinics. Therefore, the risk of unblinding the group allocation is reduced, and patient study entry, measurement events and treatment sessions will be under control of one clinic that is responsible for study management.

The planned study is single-blinded only. In general, a sham or placebo intervention in therapeutic disciplines is not always possible. In this study, the treating therapists and patients cannot be blinded to the study group interventions. However, the assessor and the researchers performing the data analyses will be blinded to increase the study’s internal validity and to ensure a low detection bias [42].

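### The motor-decline halting criterion needs a three-level CMSA loss, which cannot occur on an arm entered at level 3 or a hand entered at level 2 or 3; it also gives no patient count and assigns nobody to compare the arms

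*Protocol article*

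**What the plan says.** Under Criteria for halting the trial, the third criterion applies when experimental-group patients show an "unexpected decrease in motor function (change of three or more levels in the Chedoke-McMaster Stroke Assessment) indicating a highly significant difference" between YouGrabber and conventional therapy. It names no subscale, number of patients, test, significance level or time of comparison. The other three criteria each carry a count: more than three patients for shoulder pain, more than half with a minimum of five for cybersickness, and at least two for seizures.

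The Secondary outcomes section says of the CMSA impairment subscales for hand and arm: "Patients will be scored on a seven-point scale". Level 1 is the floor and level 7 is no detectable impairment. Table 1 requires "Chedoke-McMaster Stroke Assessment arm subscale level ≥3 and hand subscale level ≥2", with the two subscales at least two levels apart. Table 3 schedules the CMSA at all five measurement events.

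On access to scores and allocation, the case report form is "stored in a locked cabinet and will not be accessible by the treating therapist", and the Discussion states that "the assessor and the researchers performing the data analyses will be blinded". The Randomisation section keeps allocation from the assessor until the study ends, informs the treating therapist of it, and places the list in one clinic's pharmacy. Under Quality control, anonymised data go to the study coordinator for analysis.

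**The concern.** A harm threshold expressed as a loss of levels must be reachable from the levels at which patients may enter. Here a low entry level and the floor of the scale together leave less room than the criterion demands. If a hand entered at level 3 falls to level 1, it has lost everything the scale can measure and still does not meet the criterion.

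This is the only halting criterion that covers motor deterioration, in a trial of motor training. Followed exactly, it would not respond to such losses however many experimental-group patients had them.

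The second part of the criterion adds to the difficulty. It asks for a strong difference between therapies, but the article does not say who brings CMSA scores and allocation together while the trial is running.

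**Working it through.** The plan gives no calculated figure for this criterion, so there is none to reproduce. The check is an enumeration.

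**Inputs.** Scale 1 to 7 (Secondary outcomes). Entry arm ≥ 3, hand ≥ 2, |arm − hand| ≥ 2 (Table 1). Required loss ≥ 3 levels (Criteria for halting the trial). Loss is counted from the entry level, because the article names no other reference point.

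**Step 1: room to fall.** Largest possible loss = entry level − 1.
- Arm 3: 3 − 1 = 2
- Hand 2: 2 − 1 = 1
- Hand 3: 3 − 1 = 2
- Any subscale at level 4: 4 − 1 = 3, so the criterion is met only by a fall to the floor

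A loss of three levels therefore needs an entry level of 4 or more on that subscale.

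**Step 2: permitted pairs (arm, hand).** There are 16 with the gap rule applied.
- Arm cannot lose three levels: (3,5), (3,6), (3,7), which is 3 pairs
- Hand cannot lose three levels: (4,2), (5,2), (5,3), (6,2), (6,3), (7,2), (7,3), which is 7 pairs
- Both can: (4,6), (4,7), (5,7), (6,4), (7,4), (7,5), which is 6 pairs

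So 3 + 7 = 10 of 16 pairs have one subscale on which the criterion cannot be met. None has two.

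**Step 3: sensitivity to level 7.** Table 1 asks for a persistent deficit of arm and hand, and level 7 means no detectable impairment. If level 7 is therefore excluded on both subscales, 9 pairs remain: (3,5), (3,6), (4,2), (4,6), (5,2), (5,3), (6,2), (6,3), (6,4). The arm is affected in 2 and the hand in 5, so 7 of 9. Again no pair has both subscales affected.

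**Step 4: the comparison clause.** The reading of the clause decides how many patients are needed. Assume 30 per arm (60 recruited, equal groups), no events in the control group and a two-sided Fisher exact test:

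| Experimental-group patients with the decline | p |
|---|---|
| 5 | 0.052 |
| 6 | 0.024 |
| 7 | 0.0105 |
| 8 | 0.0046 |

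If the clause means p < 0.05, six patients are needed; if it means p < 0.01, eight. Read patient by patient, one would do. The article does not say which reading applies, and these levels are assumptions used only to show the spread.

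**Step 5: who can apply it.** The assessor holds the scores without the allocation. The analysts are blinded. The treating therapist has the allocation without the case report form. The pharmacy has the list without the scores. The coordinator receives the data, and the article does not state whether that role is blinded. No section gives any of them the task.

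**The case against.** A reader might infer that the criterion can never be met. The documents do not support that. The criterion names no subscale, and because of the gap rule every eligible patient has at least one subscale at level 4 or higher that can fall three levels. The only pairs with no route to the criterion, (3,2) and (3,3), break the gap rule and so are not eligible.

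A reader might also infer that nobody could compare the arms. That goes too far as well. The coordinator receives the data and is not said to be blinded, the pharmacy could supply the allocation, and blinded analysts can compare coded groups. The accurate statement is that nobody is assigned. An article may leave a test, an interim look or a monitoring role to the full protocol, so these gaps would not be a finding alone.

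Three further objections have weight. The 10 of 16 counts combinations, not patients. Halting the trial is not the only safeguard: adverse events go directly to the ethics committee, unexpected events are documented and sent to the coordinator, and the physician on duty is informed. The three levels might also be meant as a sum over arm and hand. The article describes no such sum, and even under that reading a decline confined to an affected subscale totals at most two levels and would not meet the criterion.

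None of this removes the mismatch between the stated threshold, the scale floor and the entry levels.

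**Conclusion.** The point holds in a limited form. The halting criterion does not fit the CMSA floor and the permitted entry levels: on one subscale in 10 of 16 permitted pairs (7 of 9 if level 7 is excluded), no decline of any size can meet it. It can still be triggered through the other subscale in every eligible patient, so the gap is in what it registers. How many patients are affected is unknown, because the distribution of entry levels is not given. The result assumes that loss is counted from the entry level and that a level refers to a single subscale.

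The missing patient count, the undefined strength of the between-therapy difference and the unassigned comparison are secondary. They matter because they sit in the same sentence and leave it open to opposite decisions on the same data.

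**What to change.** Reconcile Criteria for halting the trial with Table 1 and the CMSA description, so that motor decline can be registered on each subscale at every permitted entry level. In the same sentence, state which subscale or subscales are meant, how many patients are needed, and what the between-therapy difference refers to. No threshold is proposed here; it is for the investigators and ethics committees.

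Name an existing role to review CMSA declines by arm after each measurement event, using the pharmacy's list. The study coordinator or the sponsor's authorised person are candidates. If the coordinator also analyses the data, the choice must be squared with the stated blinding of the analysts.

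The cost is protocol wording, a notification to the ethics committees and a reporting line. It adds a duty to an existing role (the sponsor's authorised person is now described only for up to three monitoring events per centre), but no patients, visits or staff.
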